## **9 ASSESSMENT OF SAFETY**

### **9.1 Specification of Safety Parameters**

The operative and non-operative treatments in this trial are standards of usual care. The Adverse Events (AEs) and Serious Adverse Events (SAEs) are therefore those inherent to standard of care treatments. Safety parameters will be recorded in our online data capture system (REDCap). These parameters include the date of occurrence of AE/SAE, a detailed description of the nature of the event, assessment, follow up, and the resolution of the AE/SAE, as appropriate to the event. The safety procedures will be performed for our primary study/trial that ends at one (1) year of follow up and not for the sub-study. Further details are provided in the sections below.

#### **9.1.1 Unanticipated Problems**

Unanticipated problems include breach of confidentiality or loss of data. Safeguards to prevent this include storage of data in locked file cabinets, use of password protected REDCap databases, use of courier service with tracking for transfer of MRI discs with PHI to the data coordinating center at VUMC, and restricting access to data by authorized study personnel only.

#### **9.1.2 Adverse Events (AEs)**

AEs for this trial include:

- Post-operative infection
- Post-operative bleeding
- Nerve injury
- Complications due to anesthesia
- Adhesive capsulitis (frozen shoulder)

#### **9.1.3 Serious Adverse Events (SAEs)**

SAEs for this trial include:

- Death
- Event requiring hospitalization (in-patient admission) related to treatment

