## 9.3 Characteristics of an Adverse Event

### 9.3.1 Relationship to Study Intervention

Study PI will assess relationship to study intervention. To assess relationship of an event to study intervention, the following guidelines will be used:

1. Related (Possible, Probable, Definite)
  - a. The event is known to occur with the study intervention.
  - b. There is a temporal relationship between the intervention and event onset.
  - c. The event abates when the intervention is discontinued.
  - d. The event reappears upon a re-challenge with the intervention.
2. Not Related (Unlikely, Not Related)
  - a. There is no temporal relationship between the intervention and event onset.
  - b. An alternate etiology has been established.

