### **9.4.2 AEs & Unrelated SAEs**

Anticipated AEs or unrelated SAEs will be handled in a less urgent manner but will be reported to the DSMC, IRB, and funding agency (PCORI). All individual AE and Safety reports will be maintained by the investigator and a summary (not individual reports) of all adverse events that have occurred within the last approval period that are associated with the study, whether related or non-related, will be submitted to the IRB at the time of continuing review. These reports will also be submitted to the DSMC and the funding agency (PCORI) during the yearly DSMC meetings.

Adverse events may include a participant's death as a result of a longtime illness (non-related), a breach in confidentiality, or any complaint of a participant unless the risk involved is serious (in which case, the event is reported as an unanticipated problem involving risk to participants or others or as a serious adverse event at the time of occurrence).

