## **9.5 Halting Rules**

While the comparison of treatment arms is novel, the actual therapy in each treatment arms is not. All procedures are standardized, and potential adverse events are well understood. The surgery is an outpatient procedure with very low risk. Nonetheless, a continuous monitoring rule for monitoring SAE has been developed for the DSMC to ensure the SAE rate does not exceed 10%.

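### For hospitalizations, Section 9.1.3 makes relatedness part of the SAE definition, while 9.3.1 and 9.4 grade it afterwards, so a non-fatal admission judged unrelated falls outside both event lists

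*Protocol*

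**What the plan says.** **Definitions.** Section 9.1.3 opens with "SAEs for this trial include" and gives two items. Death carries no qualifier. The other item is "Event requiring hospitalization (in-patient admission) related to treatment". Section 9.1.2 opens with "AEs for this trial include" and names five treatment complications, with no general term for other medical events.

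**Grading.** Section 9.3.1 has the study PI class an event as related or not related, using guidelines. One item under the related class is "The event reappears upon a re-challenge with the intervention".

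**Reporting.** Section 9.4.1 expedites SAEs that are, among other things, possibly related to the research procedures. Section 9.4.2 says "Anticipated AEs or unrelated SAEs will be handled in a less urgent manner but will be reported to the DSMC", and asks for a summary of adverse events "that are associated with the study, whether related or non-related, will be submitted to the IRB at the time of continuing review".

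**Use of the count.** Sections 9.5 and 12.3.4 describe a continuous monitoring rule for the DSMC "to ensure the SAE rate does not exceed 10" per cent.

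**Masking.** Section 5.4.2 says that the arms are not masked. Section 5.4.1 says that the PI is e-mailed whenever a participant is randomized.

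**The concern.** Seriousness and causality are normally settled in sequence: an event is recorded because of what happened, and someone then judges the cause. For admissions, 9.1.3 merges the two steps. If the judgement comes first, an admission thought unrelated need not enter the record as an SAE, and the AE list has no place for it either.

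The person making the judgement knows the arm. The result feeds the only halting criterion for which the protocol gives a figure. If admissions judged unrelated are left unrecorded, the DSMC sees only those already classed as related and has no means of checking the calls that removed the others.

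**Working it through.** **1. The sections side by side**

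| Section | Where relatedness enters |
|---|---|
| 9.1.3, death | Not part of the definition |
| 9.1.3, admission | Part of the definition |
| 9.3.1 | Graded by the study PI; a not-related class is provided |
| 9.4.1 | A further filter on events that are already SAEs |
| 9.4.2 | Unrelated SAEs are a reporting class of their own |

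For an admission that is already an SAE, the not-related class in 9.3.1 has nothing left to describe, and the possibly-related filter in 9.4.1 is close to redundant. The unrelated SAEs of 9.4.2 can then only be unrelated deaths.

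**2. A non-fatal admission judged unrelated.** It is not death and it fails the qualifier on the second item of 9.1.3. Unless it happens to be one of the five complications in 9.1.2, it is not a listed AE. Neither list calls for it.

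**3. Timing.** Section 9.2 starts recording at informed consent, while 6.3.1 and 6.3.2 allow up to 8 weeks after randomization for surgery or for non-operative physical therapy to start. An admission before any treatment can hardly be related to treatment, so in that interval essentially only deaths meet 9.1.3.

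**4. The guide to causality.** Two of the four items for the related class in 9.3.1 are that the event abates when the intervention is discontinued and that it recurs on re-challenge. Neither can be observed for a one-time operation. The section does not say how many items are needed.

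**5. Number of admissions affected.** The protocol gives no admission rate. Assume that 5-15% of participants have one non-fatal admission in the year that would be judged unrelated:

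- 700 × 0.05 = 35
- 700 × 0.15 = 105

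**6. Bearing on the 10% rule.** The 10% figure is a design choice and there is nothing to reproduce. The sequential boundary is not in the protocol, and the DSMC charter is a separate document. As a rough illustration only, take the chance that the final observed proportion in 700 participants exceeds 10%, that is P(X ≥ 71) with X ~ Binomial(700, p). Assume deaths plus related admissions at 1-2%, and add the assumed unrelated admissions:

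| Unrelated admissions (assumed) | Total p | Expected events | P(observed > 10%) |
|---|---|---|---|
| Not counted | 1-2% | 7-14 | about 0 |
| 5% | 6-7% | 42-49 | at most 0.0013 |
| 8% | 9-10% | 63-70 | 0.16-0.47 |
| 10% | 11-12% | 77-84 | 0.78-0.94 |
| 15% | 16-17% | 112-119 | about 1 |

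Over part of this assumed range, whether unrelated admissions are counted settles whether 10% is exceeded. This cuts both ways. Leaving them out hides them, but counting them all would make the 10% ceiling measure a different rate.

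**The case against.** Several stronger readings are tempting, and the protocol does not support them.

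- **That 9.1.3 and 9.4.2 contradict each other.** Section 9.4.2 asks for unrelated SAEs, not unrelated admissions, and its one example of an unrelated medical event is a death from long illness. Unrelated deaths keep that class non-empty, so both sections can be obeyed. It is a mismatch.
- **That an unrelated admission can never be an SAE.** Both lists are introduced as inclusive and are not expressly closed.
- **That sites screen events out before recording.** Section 9.3.1 gives the judgement to the study PI. Section 7.4.1 has staff notify the PI and complete an event report when a participant reports an SAE, with no relatedness screen first. Section 16.1.1 has sites report on becoming aware. Some unrelated admissions may therefore be recorded in practice. The questionnaire wording and the operations manual are not shown, so it can be said only that these events need not be recorded.
- **That no surgical admission could qualify because all four items must hold.** The items are called guidelines and the related class runs from possible to definite. Hospital readmission is also a listed risk of surgery in 2.4.1.
- **That the known-to-occur item conflicts with 9.4.1.** Section 9.3.2 lets severity or frequency make a known event unexpected.
- **That a planned comparison of harms between arms is spoiled.** Sections 3 and 12 plan no comparison of admissions.

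It can also be said that both arms are standard care, which is the protocol's stated reason for confining safety events to those inherent in the treatments. That supports a short AE list. It does not explain why causality should be settled inside the definition of an SAE and then graded again.

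**Conclusion.** The point holds for hospitalizations and not for deaths. Section 9.1.3 makes relatedness a condition of seriousness, the later sections assume that it is judged separately, and a non-fatal admission judged unrelated has no listed place. In an open trial, one judgement made with knowledge of the arm therefore decides which admissions need be recorded, reach the DSMC and count toward the 10% rule.

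That conclusion rests on the wording alone. Its size cannot be derived. The 35-105 admissions and the probabilities above depend entirely on assumed rates and on a simple fixed-sample tail, not on the DSMC's own boundary. The matter should be corrected, but it does not touch the primary efficacy analysis.

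**What to change.** - **9.1.3:** delete the relatedness qualifier, so that every in-patient admission in the first year is recorded as an SAE.
- **9.3.1:** grade relatedness after recording, and note that the discontinuation and re-challenge items cannot apply to a one-time operation.
- **DSMC reports (16.4.3):** list all admissions by arm together with the PI's classification, so that the calls can be reviewed.
- **9.5 and 12.3.4:** state which of the recorded events the 10% rule counts, so that background admissions do not silently change its meaning. If all admissions are to count, the 10% ceiling needs a fresh justification.

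If the rule continues to count only related admissions, the PI's judgement stays in that count. The gain is then that the DSMC can see and question it.

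The cost is protocol wording and extra event reports. Their number is unknown; 35-105 is the figure under the assumption above. Section 9.2 already has participants asked about AEs and SAEs on each first-year questionnaire, so no new contact point is needed.

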### **9.3.3 Severity of Event**

The study PI will determine severity of event. The following scale will be used to grade adverse events:

1. Mild: no intervention required; no impact on activities of daily living (ADL)
2. Moderate: minimal, local, or non-invasive intervention indicated; moderate impact on ADL
3. Severe: significant symptoms requiring invasive intervention; subject seeks medical attention, needs major assistance with ADL

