#### **12.3.4 Safety Review**

A continuous monitoring rule for monitoring SAE has been developed for the DSMC to ensure the SAE rate does not exceed 10%.

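### Section 9.1.3 names only death and treatment-related admission as SAEs, so a lasting disability managed without admission escapes the 10% SAE rule and the other SAE-triggered steps

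*Protocol*

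**What the plan says.** - **SAE list (9.1.3).** It opens with "SAEs for this trial include" and has two entries: death, and "Event requiring hospitalization (in-patient admission) related to treatment". No other criterion follows.
- **AE list (9.1.2).** Nerve injury and "Complications due to anesthesia" are listed here, with no statement of when either becomes serious.
- **Severity scale (9.3.3).** The top grade is "Severe: significant symptoms requiring invasive intervention; subject seeks medical attention, needs major assistance with ADL". Nothing links a grade to seriousness.
- **Halting rule (9.5).** It states that "The surgery is an outpatient procedure with very low risk" and that "a continuous monitoring rule for monitoring SAE has been developed for the DSMC to ensure the SAE rate does not exceed 10" per cent. Section 12.3.4 repeats the ceiling.
- **Steps that depend on the SAE label.** These are immediate contact with the study PI and coordinator when a questionnaire reports an SAE (7.4.1), a 30-day rather than 7-day recording window after the end of participation (9.2), and event reporting within 7 calendar days (9.4.1, 9.4.3).

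**The concern.** An admission-based test of seriousness is least sensitive where the procedure is outpatient. The lasting harm that a reader would most want monitored after shoulder surgery is disability, and nerve injury is the example the protocol itself names. A palsy that never resolves but is managed in clinic meets neither entry in 9.1.3.

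What is at stake is safety oversight, not the efficacy analysis. The only quantitative safety boundary in the protocol counts SAEs. An event outside the definition cannot move that count, however grave its consequences, and it misses the faster handling that the SAE label brings. Section 16.6.2 also makes failure to report an SAE a protocol violation, so sites need a clear boundary between AE and SAE.

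**Working it through.** The 10% is a chosen ceiling. The protocol gives no boundary, error rate or look schedule for the rule, so there is no derived figure to reproduce. The check is a comparison of sections, followed by an illustration on assumed values.

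**1. Follow one event through the text.** Take a nerve injury with lasting loss of function, treated without admission and not fatal.

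| Section | Question | Answer as written |
|---|---|---|
| 9.1.3 | Death or treatment-related admission? | No, so not an SAE |
| 9.1.2 | Listed AE? | Yes |
| 9.3.3 | Does a severe grade make it serious? | No such link |
| 9.5, 12.3.4 | Counted by the 10% rule? | No |
| 7.4.1 | Immediate contact with the study PI? | No; an event report is completed |
| 9.2 | Recording window after participation ends | 7 days, not 30 |
| 9.4.1, 9.4.3 | Eligible for 7-day reporting if unexpected? | No; an unanticipated problem that is not an SAE goes to annual review and DSMC meetings |
| 16.4.3 | Seen by the DSMC? | Yes, as an AE, in reports every 6 to 12 months |

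The window differs only for events starting in the 30 − 7 = 23 days between the two limits. That matters mainly for patients operated on late, for example after the crossover that 5.3.2 allows at any time.

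**2. Is the 9.1.3 list open or closed?** Where the protocol means a list to be open it says so: Table 1 and section 5.2 state that their examples are not limiting, and 16.6.1 and 16.6.2 state that theirs are not exhaustive. Section 9.1.3 carries no such marker. Even on an open reading it supplies no criterion for judging an unlisted event.

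**3. Scale of the ceiling.** With the 700 patients (350 per arm) of section 12.3.3, 10% is 0.10 × 700 = 70 patients overall, or 0.10 × 350 = 35 in one arm. The protocol does not say which denominator applies.

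**4. Illustration only.** Let p be the true rate of serious events and f the share managed without admission. Both are assumptions; the documents give neither. The counted rate is p × (1 − f), which reaches 10% when p = 0.10 / (1 − f):

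- f = 10%: 0.10 / 0.90 = 11.1%
- f = 25%: 0.10 / 0.75 = 13.3%
- f = 50%: 0.10 / 0.50 = 20.0%

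With an assumed p of 15%, the exact binomial probability that the final count exceeds 10% is:

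| f | Counted rate | More than 35 of 350 | More than 70 of 700 |
|---|---|---|---|
| 0 | 15.0% | 0.996 | 1.000 |
| 10% | 13.5% | 0.971 | 0.997 |
| 25% | 11.25% | 0.740 | 0.838 |
| 50% | 7.5% | 0.035 | 0.007 |

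This is a single count at full enrolment, not the DSMC's continuous boundary. It shows the direction of the effect and that it depends on f. It does not estimate the undercount.

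**The case against.** The case on the other side is substantial, and much of it limits the point.

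- **The list says that SAEs include the two items.** It could be read as open, and a listed AE that leads to treatment-related admission does become an SAE. This stands as a matter of language, but it leaves sites without a test of seriousness.
- **The event is not hidden.** A reader might infer that it would surface only in a yearly summary. The documents do not support that. Sites report AEs on becoming aware of them (16.1.1), each AE reported on a questionnaire gets an event report (7.4.1), events are followed to resolution or stabilization (9.2), and AEs are in the DSMC reports prepared every 6 to 12 months (16.4.3).
- **Relabelling would not by itself bring 7-day reporting.** Sections 9.4.1 and 9.4.3 also require the event to be unexpected or unanticipated, and nerve injury is a disclosed risk (2.4.1). It would qualify only if its nature, severity or frequency departed from the risk information (9.3.2). The narrow definition closes the route even then.
- **No between-arm SAE comparison is planned.** A reader might infer that such a comparison would be biased, but section 12 describes none.
- **There is another escalation route.** Section 9.4.2 names "any complaint of a participant unless the risk involved is serious" among its examples, and sends the serious case to SAE or unanticipated-problem reporting. That permits judgement in an individual case, but seriousness is not defined there and the sentence concerns unrelated deaths, confidentiality breaches and complaints.
- **The DSMC charter is not at hand.** It may say what the rule counts. But the protocol places the charter outside itself, among its supplemental materials, and it is section 9 that defines an SAE for the sites.
- **The numbers are assumed.** A true rate of 15% sits uneasily with surgery the protocol calls very low risk. Agreed; the illustration carries no weight as an estimate.

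**Conclusion.** The point holds as a narrow definition with identifiable consequences. As written, a persistently disabling event managed without admission is outside the 10% SAE count, immediate contact with the study PI, the 30-day recording window and any access to 7-day reporting. It remains a recorded AE that the DSMC can see. Lasting nerve injury is the case that carries weight; a life-threatening event managed without admission is equally outside the list but probably rarer.

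The size is unknown because the documents give no complication rates. The conclusion rests on reading the two entries in 9.1.3 as the definition, and on the DSMC rule using that definition. No sample size, power or type I error figure is affected. A reader might also infer that every severe AE needing an invasive intervention ought to be serious. The documents do not support that step: they treat severity (9.3.3) and seriousness (9.1.3) as separate attributes, and merging them would enlarge the count without re-examining the ceiling.

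**What to change.** 1. In 9.1.3, add three SAE criteria to the existing two: life-threatening event; persistent or significant disability, including unresolved nerve injury; and prolonged hospitalization.
2. Use the same definition in 7.4.1, 9.2, 9.4.1 to 9.4.3 and the DSMC monitoring rule (9.5, 12.3.4).
3. Ask the DSMC to confirm that its 10% boundary still fits the wider definition, since more events can then enter the count.

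The cost is a wording amendment, an update to the event form and a few more SAE reports.

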## 9.2 Time Period and Frequency for Event Assessment and Follow-Up

All reportable events will be recorded in the study record with start dates occurring any time after informed consent is obtained until 7 days (for non-serious AEs) or 30 days (for SAEs) after the last day of study participation for the main study (1 year of follow-up). Subjects will be asked about the occurrence of AE/SAEs on each follow-up questionnaire in the first year.

Events will be followed for outcome information until resolution or stabilization, as appropriate. Unanticipated problems will be recorded in the data collection system throughout the study as discovered.

## 9.3 Characteristics of an Adverse Event

### 9.3.1 Relationship to Study Intervention

Study PI will assess relationship to study intervention. To assess relationship of an event to study intervention, the following guidelines will be used:

1. Related (Possible, Probable, Definite)
  - a. The event is known to occur with the study intervention.
  - b. There is a temporal relationship between the intervention and event onset.
  - c. The event abates when the intervention is discontinued.
  - d. The event reappears upon a re-challenge with the intervention.
2. Not Related (Unlikely, Not Related)
  - a. There is no temporal relationship between the intervention and event onset.
  - b. An alternate etiology has been established.

### 9.3.2 Expectedness of Event

The Study PI will be responsible for determining whether an adverse event is expected or unexpected. An adverse event will be considered unexpected if the nature, severity, or frequency of the event is not consistent with the risk information for the intervention.

### **9.3.3 Severity of Event**

The study PI will determine severity of event. The following scale will be used to grade adverse events:

1. Mild: no intervention required; no impact on activities of daily living (ADL)
2. Moderate: minimal, local, or non-invasive intervention indicated; moderate impact on ADL
3. Severe: significant symptoms requiring invasive intervention; subject seeks medical attention, needs major assistance with ADL

## **9.4 Reporting Procedures**

### **9.4.1 Related SAEs & Safety Issues**

The following will be reported to the IRB, the funding agency (PCORI), and the DSMC within 7 calendar days of the PI becoming aware of the event:

- Any serious adverse event that in the investigator's opinion was unanticipated or unexpected, involved risk to participants or others, and was possibly related to the research procedures
- Any noncompliance with the IRB-approved protocol that increased risk or affected the participant's rights, safety, or welfare.

